### Inclusion criteria

Patients aged 18 to 65 yearsComplete articular (AO/OTA type C) displaced distal radius fractureAcceptable closed reduction on X-ray obtained immediately after admission to the Emergency Department (<12 h) defined, according to the Dutch National Guidelines [6], as:Radial inclination ≥15°Radial height (RH, also known as radial length) = distance between lateral most radial tip and ulnar surface: >5 mm, positive height shownVolar angulation <20° or dorsal angulation <15°Articular step-off or gap <2 mm. A step-off is defined as the loss of articular congruity of the distal radius perpendicular to the articular surface and parallel to the articular surface and a gap parallel to the articular surface [23]

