### Interventions

After presentation to the Emergency Department, all patients will be treated with closed reduction and plaster immobilisation. Closed reduction will preferably be performed according to the Robert-Jones method [24] under local anaesthesia by means of a haematoma block with 20 cc Lidocaine 1 %. First continuous traction will be applied. Afterwards the deformity will be manually reduced and the wrist and hand will be immobilised in the reduced position. To verify the success of reduction, additional radiographs will be performed (see inclusion criteria). After adequate reduction has been confirmed, the wrist will be immobilised initially in a below-the-elbow single-cut plaster of paris, according to the Dutch guidelines [6]. After informed consent has been obtained, patients will be randomised either into the intervention group (ORIF) or into the control group (plaster immobilisation).

The control group will continue with plaster immobilisation. After approximately one week the single-cut plaster will be changed into a circular forearm plaster for five weeks immobilisation in total, according to the Dutch guidelines [6]. During plaster immobilisation advice and instructions on moving the uninvolved joints will be given. This includes flexion of the elbow and movement of the metacarpophalangeal (MCP) joints, the proximal interphalangeal (PIP) joints and the distal interphalangeal (DIP) joints. Additionally patients will be instructed to keep the arm high, preferably in a sling.

The intervention group will be treated with open reduction and locking plate fixation. All fractures will be fixed internally with a volar locking plate. This method employs a volar approach to the distal radius, according to Henry [25]. This approach implies an incision between the tendon of the flexor carpi radialis muscle and the radial artery. The advantages of the volar approach are the possibility of an uncomplicated extension of the distal part of the forearm and an optimal cover of the plate by soft tissue [26]. Furthermore, using this technique, the median nerve is not at risk. Additionally, fixation with a volar locking plate can be supported by a dorsal plate or radial column plate. This will be at discretion of the surgeon and depends on the fracture configuration and the position of the fragments. The same applies to the type and brand of the locking plate. Fracture reduction and screw placement will be fluoroscopically confirmed.

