**Fig. 1 Fig1:**
[figure not shown]
Follow-up visitsRange of motion (ROM) of the wrist measured with a handheld goniometer of both the injured as the healthy wrist. ROM measurements will start in both groups at the third follow-up (at 5/6 weeks) (Fig. 1). In the control group, this will be the moment the plaster immobilisation ends. ROM measurements include pronation and supination, ulnar and radial deviation and palmar and dorsal flexion of the wrist.Grip strength, which will be measured on both sides with a Baseline dynamometer as the mean of three measurements. The difference in grip strength will be calculated as a percentage of the uninjured side. Grip strength measurements will start in both groups at the third follow-up (at 5/6 weeks) (Fig. 1).Radiographic parameters, such as radial inclination, radial length, volar or dorsal tilt and articular step-off and/or gap. This will be measured digitally in the Picture Archiving and Communication System (PACS) of the participating hospital on standard X-rays of the wrist. Radiographs will be obtained according to standardised procedures in three directions; posterior-anterior (PA), lateral carporadial and lateral. Radiographs will be performed at all follow-up visits.Number of crossovers. Crossovers include all patients who were randomised to treatment with plaster immobilisation (control group), but who require operative treatment due to loss of reduction during the first six weeks. Loss of reduction is defined as any displacement that no longer meets the previously mentioned inclusion criteria for acceptable reduction.The occurrence of complications, such as complaints in plaster, loss of reduction, superficial infection of the wound or deep infection of the plate, compartment syndrome, complex regional pain syndrome (CRPS) type 1 according to the Veldman [33] and the Budapest criteria [34, 35], tendinitis or rupture of the tendon, non-union, malunion, carpal tunnel syndrome and osteosynthesis material-related complications will be recorded.Cost-effectiveness and cost-utility measured with an economic evaluation questionnaire based on the EQ-6D and the Standard Form Health and Labour questionnaire. The aim of this economic analysis is to evaluate and compare the cost-effectiveness and cost-utility of closed reduction followed by plaster immobilisation and ORIF with a plate from a societal perspective. The SF-6D will be used to express the effect of quality of life in Quality Adjusted Life Years (QALY).

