### Randomisation

All patients diagnosed with a displaced complete articular AO/OTA type C distal radius fracture will be invited to participate in this study. Patients will be approached by the investigators to participate in this study after adequate reduction of the fracture has been obtained. Patients will receive a patient information sheet with both the contact information of the coordinating investigator and the independent expert. Possible participants will have till the first outpatient appointment to decide to participate or not. This first outpatient appointment will be about 7 days after the initial trauma. If a patient decides to participate, oral and written informed consent will be obtained. Possible participants can be approached and included in this study up to the first outpatient visit.

After obtaining informed consent, patients will be randomised into either the intervention group (open reduction and plate fixation) or the control group (closed reduction and plaster immobilisation). In order to avoid any potential imbalances between the two treatment groups, patients will be randomised in two strata according to age: 18 to 40 and 41 to 65 years.

To ensure concealment of allocation, randomisation will be performed by means of a mixed block, computerised randomisation. The distribution and order of the block sizes are unknown to the researchers, who therefore remain blinded to the allocation of the next subject throughout the whole study. Surgery will be performed within two weeks after randomisation. All the participating centres can perform the randomisation on the study website (www.viparstudie.nl), where each centre has his own personal username and password. After randomisation the allocation is shown on the website.

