All patients will be analysed according to the results of the randomisation (intention-to-treat). Patient characteristics at baseline, such as gender and age, will be described by general descriptive statistics. Differences in the primary outcome (PRWE at one year) between the two groups will be analysed using the Unpaired *T*-test (if normally distributed) or the Mann–Whitney *U* test (if not normally distributed). Trends in PRWE-scores among the different time points will be assessed using multiple linear regression. The secondary outcomes; DASH-scores, quality of life (SF-36), pain (as indicated on a Visual Analogue Scale (VAS)), range of motion (ROM) and grip strength will be analysed in a similar manner. Differences between the two treatment groups in radiological outcomes, crossovers and complication rates will be analysed using the Chi-square test or the Fischer’s Exact test (in case the expected incidence was less than five). Subgroup analyses will be performed on gender and age (18 to 40 years and 41 to 65 years) for all outcomes.

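### The test named for the radiographic outcomes cannot use the pre-randomisation post-reduction values of the same four parameters, at a cost in precision that is real but probably modest

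*Protocol article*

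**What the plan says.** All places are in the protocol article.

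- **Outcomes.** The radiographic secondary outcomes are "Radiographic parameters, such as radial inclination, radial length, volar or dorsal tilt and articular step-off and/or gap". Films are taken at every follow-up visit and measured digitally.
- **Inclusion criteria.** The same four parameters define an acceptable closed reduction on the Emergency Department film: "Radial inclination ≥15" degrees; "Radial height (RH, also known as radial length") above 5 mm; volar or dorsal angulation within stated limits; and "Articular step-off or gap <2 mm".
- **Randomisation.** The film comes before allocation: "Patients will be approached by the investigators to participate in this study after adequate reduction of the fracture has been obtained". Consent and randomisation follow. The only balancing factor is age: "patients will be randomised in two strata according to age: 18 to 40 and 41 to 65 years".
- **Interventions.** After allocation, "The intervention group will be treated with open reduction and locking plate fixation", so the starting position is altered in that arm.
- **Sample size calculation and data analysis.** "Differences between the two treatment groups in radiological outcomes, crossovers and complication rates will be analysed using the Chi-square test", or Fisher's exact test where expected counts are small. No baseline term is named for these outcomes.

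**The concern.** Each radiographic outcome has a counterpart obtained before randomisation. Under plaster, the later position develops from the post-reduction position, so the first film may predict the later one. Neither the design nor the named test uses that information: allocation is stratified on age alone, and a Chi-square test has no place for a covariate.

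Two things are at stake. The interval around the radiographic treatment difference is wider than the data require. And if the arms happen to start apart, part of that gap stays in the estimate from this single trial.

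This is separate from using a test for categories on angles and millimetres. Replacing the Chi-square test with a t-test would leave the baseline value just as unused.

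**Working it through.** **The plan's own figure.** No number is given for the radiographic outcomes; the only sample size is for the PRWE. With a difference of 14, SD 17, power 90%, and alpha read as 0.05 two-sided (it is printed with a percent sign and sidedness is not stated), the normal approximation gives 31 per arm. The t-based calculation gives 31.98, so 32 per arm and 64 in total, as stated. The present point does not touch that figure.

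**Inputs.** 45 patients per arm (sample size section). The within-arm correlation rho between post-reduction and follow-up value is not in the article, so a range is assumed.

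**Chance imbalance at baseline.**
- SE of the difference in baseline means = sqrt(2/45) = 0.211 SD.
- 95% range = ±1.96 × 0.211 = ±0.41 SD.
- Probability that the arms start more than 0.3 SD apart = 15%.
- Shift carried into the follow-up comparison ≈ rho × imbalance. For 0.3 SD and rho 0.2 to 0.5, this is 0.06 to 0.15 SD. For 0.41 SD and rho 0.3 to 0.5, it is 0.12 to 0.21 SD.

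**Precision, same rho in both arms.** Variance after adjustment = (1 − rho²) × unadjusted variance; equivalent unadjusted N = 90/(1 − rho²).

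| rho (assumed) | variance removed | 90 patients count as |
|---|---|---|
| 0.2 | 4% | 94 |
| 0.3 | 9% | 99 |
| 0.4 | 16% | 107 |
| 0.5 | 25% | 120 |

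**Precision, different rho by arm.** Take 0.5 under plaster and 0 after plating, with equal baseline variances. The common slope is (0.5 + 0)/2 = 0.25. Residual variances are 1 − 2(0.25)(0.5) + 0.25² = 0.8125 (plaster) and 1 + 0.25² = 1.0625 (plate), mean 0.9375. About 6% of variance is removed, and 90 patients count as 90/0.9375 = 96.

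**Simulation.** 6,000 runs per scenario and 40 per arm (45 less 10% loss is about 40). The Chi-square cut-point was placed 0.25 SD below the plaster mean.

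| scenario | unadjusted t-test | adjusted model | Chi-square on cut-point |
|---|---|---|---|
| no effect, rho 0.5 both arms | 4.4% | 4.9% | 5.2% |
| no effect, rho 0.5 plaster, 0 plate | 5.0% | 4.8% | 5.2% |
| 0.6 SD effect, rho 0.5 both arms | 76% | 86% | 51% |
| 0.6 SD effect, rho 0.3 both arms | 75% | 80% | 52% |
| 0.6 SD effect, rho 0.5 plaster, 0 plate | 76% | 78% | 52% |
| 0.6 SD effect, rho 0.3 plaster, 0 plate | 75% | 76% | 51% |

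The adjusted model had no arm-by-baseline term. It kept its error rate even where the slopes differed.

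**The case against.** **A stronger reading is tempting:** that chance differences in starting position will be read as a treatment effect, so the radiographic comparison is biased or prone to false positives. The article does not support this. Allocation is random, so the unadjusted comparison is right on average and its standard error already allows for chance imbalance; the simulated error rates above show it. Only about rho times an imbalance carries through, not the whole of it.

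**The planned comparison may be of categories.** The Outcomes section defines loss of reduction as no longer meeting the entry limits. On that scale every patient starts as acceptable, and no imbalance is possible. This stands for that scale. It does not make the first film uninformative: against the 15° limit for radial inclination, a wrist entering at 16° fails after losing just over 1°, one entering at 22° only after losing just over 7°.

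**The correlation may be low.** Entry limits truncate the baseline range and plating re-reduces the fracture. The Background cites redisplacement of up to almost 60% under plaster. The Discussion calls linear PACS measurements less exact. All of this stands, and it is why the lower gains are the more credible ones.

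**The Chi-square test is the larger fault.** In the simulation it cost about 25 power points against the t-test, while leaving out the baseline cost 1 to 10. This also stands, but curing the first does not cure the second.

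**Covariates are often left to an analysis plan.** That plan is not shown and may contain an adjusted model. But the article does not leave the method open: it names a test, and that test is unadjusted.

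**Conclusion.** The point holds as a matter of efficiency, not validity. All four named radiographic outcomes have a value before randomisation, and the stated comparison cannot use it.

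The size depends on a correlation that the article does not give. Adjustment removes 4% to 25% of the variance for an assumed common rho of 0.2 to 0.5, and about 6% if the first film predicts the later one only under plaster (power about 76% to 78% for a 0.6 SD effect). The gain is therefore probably modest. It concerns secondary outcomes only; the PRWE comparison, the sample size and the type I error are unaffected. The change is still worth making, because it costs little and protects the estimate in this one trial against an unlucky split of starting positions.

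**What to change.** For each continuous radiographic parameter, state a linear model with treatment arm, age stratum and the post-reduction value of the same parameter. Report the adjusted mean difference with its 95% CI. For step-off/gap, use robust standard errors, because the values are bounded and skewed. Leave out an arm-by-baseline term: with equal allocation it adds essentially no precision and spends a parameter. The same sentence replaces the Chi-square test for these measurements; that test can stay for outcomes that are truly categories.

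The cost is one sentence of analysis wording and some data work. Eligibility requires only that limits be met, and the article does not say that exact values are kept. They must be recorded in the trial database, or read from the stored films where only compliance with the limits was noted.

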### Outcomes

The primary outcome of this study is wrist pain and function expressed on the Patient-Rated Wrist Evaluation Score (PRWE) at one year follow-up. The PRWE is a validated questionnaire for assessing functional outcome and pain in patients with distal radius fractures [28]. In 1998 MacDermid et al. were the first to describe this score [29]. The PRWE consists of a 15-item questionnaire designed to measure two dimensions: wrist pain (*n* = 5 items) and function in activities of daily living (*n* = 10 items). Patients rate their levels of wrist pain and disability from 0 to 10 on two subscales: pain and function. The highest score on the subscale pain is 50, indicating worst pain, and the lowest score is zero, indicating no pain. The function score is the sum of the 10 items, divided by two. The total highest score is 100, indicating worst pain and severe impairment. The PRWE is the recommended questionnaire because it efficiently provides relevant data on pain and functional recovery in the affected wrist [30].

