## Discussion

Since the treatment allocation involves a surgical procedure, randomisation status will not be blinded. Our research group discussed the idea to let the researcher, who is assessing the outcomes at one year, be unaware of the treatment allocation. However this is practically not possible since all follow-up visits are realised by one or two researchers. At final follow-up, these researchers will have assessed the participants multiple times in the past year and will therefore be aware of their treatment allocation. Although this arrangement makes blinding impossible, the continuity of the observer is one of the strengths of this study and this will minimise intra-observer variation in the outcome measurements.

Additionally, for the measurement of the radiographic parameters we used the PACS of the participating hospitals. Although PACS is good to measure angles (inclination and dorsal or volar angulation) and the inter- and intra-observer reliability are substantial and moderate respectively [44], the linear measurement (radial length and gap or step-off) in PACS is less exact.

Last, due to the fact that patients will be analysed according to the intention-to-treat principle, possible crossovers will be analysed in the group they were allocated to.

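### The crossover outcome counts only plaster patients who require surgery for loss of reduction within six weeks, so it cannot describe departures from allocation up to the one-year endpoint, and its planned between-group test sets the plaster count against a built-in zero

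*Protocol article*

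**What the plan says.** The list of secondary outcomes in the protocol article (Outcomes, item on number of crossovers) opens its definition with "Crossovers include all patients who were randomised to treatment with plaster immobilisation (control group" and narrows it to those "who require operative treatment due to loss of reduction during the first six weeks". The next sentence gives the radiographic threshold: "Loss of reduction is defined as any displacement that no longer meets the previously mentioned inclusion criteria for acceptable reduction".

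Three other places bear on this:

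- **Outcomes, first paragraph.** The primary outcome is "wrist pain and function expressed on the Patient-Rated Wrist Evaluation Score (PRWE) at one year follow-up".
- **Sample size calculation and data analysis.** The primary analysis is by intention-to-treat. For the secondary outcomes the section states: "Differences between the two treatment groups in radiological outcomes, crossovers and complication rates will be analysed using the Chi-square test", with Fisher's exact test for small expected counts.
- **Discussion.** Under intention-to-treat, "possible crossovers will be analysed in the group they were allocated to".

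The Randomisation section allows up to two weeks between randomisation and surgery. The complications item lists loss of reduction, malunion, non-union and carpal tunnel syndrome, among others. Table 1 has cost lines for open reduction and internal fixation and for treating complications, and cost diaries run to twelve months.

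**The concern.** The intention-to-treat contrast compares early plate fixation with plaster plus whatever surgery follows. To interpret a small or null difference at one year, a reader needs to know how many patients in each arm had been operated on by then. The crossover count is the only named outcome that addresses adherence to allocation, and its definition cannot supply that number.

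Four limits are written into the rule. It runs in one direction only (plaster to surgery). It admits one reason (loss of reduction). It stops at six weeks. It turns on whether surgery is required and does not say whether an indicated but unperformed operation counts, so centres could count differently.

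The one-way definition also fits poorly with the planned between-group test, which makes sense only if both arms can produce crossovers.

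**Working it through.** **1. The protocol's own figures.** The protocol gives no expected number of crossovers, so there is none to reproduce. The sample size can be checked, to see whether the point touches it. Inputs from the sample size section: difference 14, SD 17, power 90%, and alpha read as 0.05 two-sided (the printed percent sign is taken as a slip).

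- Normal approximation: n = 2 × (1.960 + 1.282)² × 17² / 14² = 2 × 10.51 × 289 / 196 ≈ 31.0, so 31 per arm.
- Two-sample t-test version: 31.98, so 32 per arm and 64 in total, as stated.

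None of these inputs depends on how crossovers are counted. The denominator used below is the planned 45 per arm.

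**2. Who is counted.** Applying the definition as written:

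| Patient | Counted as crossover? | Recorded elsewhere? |
|---|---|---|
| Plaster, operated on in week 3 for loss of reduction | Yes | Loss of reduction is also a listed complication |
| Plaster, operated on at month 4 for malunion | No | Malunion as a complication; resource use in cost items |
| Plaster, operated on in week 3 for another reason | No | Only if the reason is a listed complication, or through cost items |
| Plaster, surgery judged necessary but not performed | Unclear | Loss of reduction as a complication |
| Allocated to plate fixation, never operated on | No | No count named |

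The window is 6/52 = 11.5% of follow-up time. That is a share of time, not of risk, because loss of reduction is not spread evenly over a year.

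**3. The between-group test.** The plate-fixation count is 0 of 45 by definition. With x plaster crossovers, the two-sided Fisher p-value is 2 × C(45, x) / C(90, x).

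- x = 5: p = 0.056
- x = 6: p = 0.026
- x = 18: p = 9 × 10⁻⁷

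For x = 5 or 6 the expected counts are 2.5 and 3 per arm, so the protocol's own rule selects Fisher's test. For x = 18 the expected count is 9, so chi-square would apply: 90 × (18 × 45)² / (18 × 72 × 45 × 45) = 22.5, which leads to the same conclusion. The value 18 is close to 0.41 × 45 = 18.45, where 41% is the conversion rate that the Background section cites from a trial in patients aged 65 and over. The null hypothesis of equal proportions can hold only if no plaster patient crosses over, so a small p-value says nothing about the treatments.

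**4. How much might be missed.** The documents give no rate for later or other-reason surgery, so the rates here are assumptions. The share captured is counted / (counted + uncounted).

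| Counted | Assumed uncounted | Operations of 45 | Share captured |
|---|---|---|---|
| 41% | 5% | 20.7 | 89% |
| 41% | 15% | 25.2 | 73% |
| 20% | 5% | 11.25 | 80% |
| 20% | 15% | 15.75 | 57% |

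If 5 to 10% of the plate-fixation arm were never operated on (also an assumption), 2.25 to 4.5 patients of 45 would be counted nowhere as departures.

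**The case against.** The strongest reply is that the protocol never offers this count as treatment received over the year. It is a narrow outcome, early conversion after failed reduction, and its window roughly matches the five weeks of plaster. The text says that crossovers *include* these patients, not that only they count. Surgery for malunion at month 4 can fairly be classed as treatment of a complication. Complications and twelve-month cost diaries record part of what falls outside. No as-treated analysis is planned, and a condensed article may leave form items to the full protocol.

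Much of this stands. A reader might infer that the plan misreports treatment received, or that it hides late surgery from the costing. The documents do not support that: no passage gives the count that role, and costs do not run through it. A reader might also infer that a film failing one criterion makes a patient a crossover. The text requires in addition that surgery be needed because of it, and the Discussion treats crossovers as people who changed treatment. The wording is loose but does not establish that reading.

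Two things remain. The counting rule is stated, not left out, and nothing in the article widens it; a complication entry is also not an operation count by arm. And the test between groups conflicts with a definition that only one arm can satisfy.

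**Conclusion.** The point holds as a limitation of a secondary outcome and as an inconsistency between its definition and its planned test. The count can describe early conversion for loss of reduction. By itself it cannot describe departures from allocation up to one year in either arm.

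The zero in the plate-fixation arm follows from the text and needs no assumption. The number of uncounted patients cannot be derived from the documents. The capture shares of 57 to 89% illustrate assumed rates, and the 41% input comes from an older population than this trial enrols.

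It would be tempting to conclude that the primary result or its power is compromised. That does not follow: the intention-to-treat PRWE comparison and the 32 per arm do not use this variable. What is at stake is how well that comparison can be interpreted when many conversions are expected.

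**What to change.** Define crossovers by treatment actually received, in both arms, to one year:

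- **Plaster arm:** each fracture-related operation performed on the injured wrist, with date and reason.
- **Plate-fixation arm:** each patient who did not have plate fixation, with reason.
- **Six-week conversions for loss of reduction:** keep as a labelled component, based on operations performed, and report the number and percentage descriptively with no test against the other arm.
- **Data analysis section:** reconcile the sentence on testing crossovers with the revised definition.

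This changes only what is counted. It leaves the intention-to-treat analysis, the sample size and the decision on who is offered surgery as they are. The cost is one revised definition and one form item (operation yes or no, date, reason). The one drawback is that the reported crossover figure may be higher.
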